## BACKGROUND

Cystic fibrosis (CF), is a rare, chronic, multisystemic disease that greatly affects the quality of life. A progressive lung dysfunction and its clinical manifestations are found in 95% of patients (CFF, 2014). These clinical manifestations are mainly related to morbidity and mortality (Alexander et al, 2014, CFF, 2014). Thus, the decrease in lung capacity and its consequences contribute to a degeneration of lung tissue, being ultimately the lung transplantation the only solution (Prados et al, 2000, CFF, 2014). Therefore, it is essential to establish an adequate treatment that prevents the progression of the lung disease. Chest physiotherapy (CPT) is one of the main approaches used to improve airway clearance, being essential in the maintenance of pulmonary function in CF due to the excess of respiratory secretions in these patients (McIlwaine et al, 2014).

Chest physiotherapy treats bronchial obstruction through airway clearance techniques administration such as deep breathing, huffing, coughing, percussions or vibrations (Pisi and Chetta, 2009; Main et al, 2011; CFF, 2014). The CPT is prescribed daily, requiring a significant commitment of time and energy for children and family members, what complicates CPT adherence (Modi & Quittner, 2006) and reduces its benefits (Sabaté, 2003; Goodfellow et al. , 2015).

Music exerts a motivational role in chronic diseases leading to psycho-emotional improvement (Le Roux et al, 2007). Music therapy (MT) interventions are usually part of integrative strategies to ameliorate some physical and/or psycho-emotional consequences in lung diseases, case of chronic obstructive pulmonary disease (Bausewein et al, 2013; Panigrahi et al, 2014). Patients reach emotional positive states reducing anxiety and depression with MT (Canga et al, 2015). In this sense, there are few music therapy interventions in CF (Goldbeck et al, 2014; Irons et al, 2014). Recently, it has been described that a carefully selected motivational music can lead to positive affective response during exercise in CF children aged from 8 to 18 (Calik-Kutukcu et al, 2016). There is only one study in CF infants and children under 2 years of age where, an appropriate music created specifically for CPT, helps to establish CPT as a routine by converting it into a positive experience (Grasso et al, 2000 ).

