**- Data collection:**

Demographic and clinical data will be collected in the case report formulary from each participant (Annex). Specifically: age, gender and respiratory infection exacerbations that requiring hospitalization.

These participants are controlled in the Pediatric Pulmonology Unit at Malaga Regional Hospital, where each child with cystic fibrosis has a detailed clinic history, being the clinical variables systematically included and the treatment updated. Therefore, the present study does not imply additional clinic information collection. Demographic and clinical information will be completed by Pediatricians during the usual follow-up.

In addition, participants will complete a baseline and 2 evaluation questionnaires during the trial-period in order to know children's and family members' chest physiotherapy perception. The questionnaires will be conducted about chest physiotherapy experiences to evaluate the evolution of their perceptions during the trial-period. These questionnaires are designed specifically to know evolution of CPT characteristics such as, enjoyment and perception or time or adherence to daily chest physiotherapy, after the use of music therapy as an adjunct to CPT (Grasso et al, 2000). The perception of pulmonary symptomatology and the impact on the quality of life will be also evaluate using a visual analog scale (VAS) to assess the magnitude of dyspnea in pulmonary diseases such as CF (Bausewein et al, 2007) and the revised cystic fibrosis quality of life questionnaire (Quittner et al, 2000), respectively.

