**- Study variables:**

- Demographics:
  - Age (quantitative variable) (unit: years)
  - Gender (qualitative, dichotomous variable) (male / female)
- Clinics:
  - Number of respiratory infection exacerbations that requiring hospitalization (quantitative variable)
  - Days of hospitalization per exacerbation (quantitative variable)
- Chest physiotherapy characteristics:
  - Use of activities to accompany the routine (qualitative, dichotomous variable) (yes /no)
  - Type of activities used to accompany the routine (toys, stories, music, radio, TV...) (qualitative variable)
- Chest physiotherapy adherence:
  - Routine frequency (quantitative variable)

- Number of times per day (quantitative variable)
- Interruptions (qualitative, dichotomous variable) (yes /no)
- Length per session (quantitative variable)
- Chest physiotherapy attitude:
  - Response to the routine using a Likert scale (-3 to +3): least enjoyment – neutral - most enjoyment (quantitative variable)
  - Feelings about the routine choosing 3 words to describe these feelings (qualitative variable)
- Perception of time taken to complete the chest physiotherapy:
  - Perception of being a long routine (qualitative, dichotomous variable) (yes /no)
  - Time that seems to need the routine (quantitative variable)
- About the music:
  - Music use frequency (quantitative variable)
  - Response to the use of music during routine using a Likert scale (-3 to +3): least enjoyment – neutral - most enjoyment (quantitative variable)
  - Usefulness of music during routine (qualitative, dichotomous variable) (yes /no)
  - How music has been useful (qualitative variable)
  - To continue using this music as an adjunct to the routine in the future (qualitative, dichotomous variable) (yes /no)
- Perception of pulmonary symptomatology and impact on quality of life:
  - Measurement of the symptoms of dyspnea using a dyspnea visual analog scale (VAS), being 1 no dyspnea and 7 maximal dyspnea.
  - Frequency of respiratory symptoms according to the revised quality of life questionnaire for cystic fibrosis during the previous 2 weeks: cough during the day and night, expectoration and type of expectoration, breathing difficulties, whistling sounds when breathing, and respiratory congestion.

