#### **- Intervention:**

After participant recruitment they will complete the baseline questionnaire and be asked to carry out the CPT routine during 6 weeks (Grasso et al, 2000; Canga et al, 2015) as follow:

- Intervention group or TG: Using the Music-CD as an adjunct to each part of the CPT routine. The Music-CD will be provided after baseline questionnaire.
- Control group without music or CG: Continuing with the usual CPT without modifications.
- Control group with music or PG: Using commercial music as an adjunct to each part of the CPT routine.

As has been comment, the CPT treatment in this Unit is divided into 3 sections with a total length of about 40 minutes: During the first part, children should be relaxed while the nebulizer inhalation treatment is applied around 10-15 minutes. Next, airway clearance techniques are administered during 20-30 minutes to promote mucus expulsion. Finally, a new relaxation phase of about 5 minutes is proposed, where antibiotic nebulizer treatment is administered if necessary.

Participants in every group will continue with their usual treatment regimen without modifications. Follow-up changes or treatments modifications are not planned in any case.

A second questionnaire will be completed after 6 weeks and participants will continue managing the CPT routine in the same way during a new 6-week period. After that, the final questionnaire will be completed (Grasso et al, 2000) and the music-CD will be offered to CG and PG participants.

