#### QUESTIONNAIRES:

☐ Chest physiotherapy characteristics:

- Use of activities to accompany the routine (yes /no)
- Type of activities used to accompany the routine (toys, stories, music, radio, TV...)

- ☐ Chest physiotherapy adherence:
  - Routine frequency
  - Number of times per day
  - Interruptions (yes /no)
  - Length per session
- ☐ Chest physiotherapy attitude:
  - Response to the routine using a Likert scale (-3 to +3): least enjoyment – neutral - most enjoyment
  - Feelings about the routine choosing 3 words to describe these feelings
- ☐ Perception of time taken to complete the chest physiotherapy:
  - Perception of being a long routine (yes /no)
  - Time that seems to need the routine
- ☐ About the music:
  - Music use frequency
  - Response to the use of music during routine using a Likert scale (-3 to +3): least enjoyment – neutral - most enjoyment
  - Usefulness of music during routine (yes /no)
  - How music has been useful
  - To continue using this music as an adjunct to the routine in the future (yes /no)
- ☐ Perception of pulmonary symptomatology and impact on quality of life:
  - Measurement of the symptoms of dyspnea using a dyspnea visual analog scale (VAS), being 1 no dyspnea and 7 maximal dyspnea ☐
  - Frequency of respiratory symptoms according to the revised quality of life questionnaire for cystic fibrosis during the previous 2 weeks:

always, often, sometimes, never

Coughing during the day..... ☐ ☐ ☐ ☐

Wake up at night because of coughing..... ☐ ☐ ☐ ☐

To expectorate (spit out the mucus)..... ☐ ☐ ☐ ☐

Mucus appearance: ☐ Watery ☐ Yellow/Transparent ☐ Yellow-Green ☐ Green/Bloody

☐ I do not know

Respiratory congestion..... ☐ ☐ ☐ ☐

Whistling sounds when breathing..... ☐ ☐ ☐ ☐

Breathing difficulties..... ☐ ☐ ☐ ☐

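### The interruptions item is one undefined yes/no answer with no recall window, so it discards how often sessions are broken off; a two-week count would keep that information

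*Combined protocol and SAP*

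**What the plan says.** The combined protocol and SAP, under Study variables, gives four items for chest physiotherapy adherence. Three are quantitative: "Routine frequency (quantitative variable"), "Number of times per day (quantitative variable") and "Length per session (quantitative variable"). The fourth is "Interruptions (qualitative, dichotomous variable) (yes /no"). The Questionnaires annex repeats it as "Interruptions (yes /no") and adds no definition, count or time frame.

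On timing, the Background states that "The CPT is prescribed daily". Under Data collection, "participants will complete a baseline and 2 evaluation questionnaires during the trial-period". Under Intervention, the baseline questionnaire precedes the study routine, "A second questionnaire will be completed after 6 weeks", and the last follows a further six weeks.

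The respiratory symptom items in the same annex are built differently. They refer to the preceding two weeks, and most use a four-level frequency scale.

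Under Statistical analysis, qualitative measures are compared by Chi-square or Fisher tests and quantitative ones by ANOVA or Kruskal-Wallis. A repeated-measures analysis is planned for change over time and a Wilcoxon test for baseline against final values within each group.

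**The concern.** Adherence to daily physiotherapy is a stated secondary objective. Of the four adherence items, only this one could record that a session was started and then broken off. The others record how often the routine is done and how long it lasts.

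The format has three weaknesses:

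- **Frequency is lost.** If a family answers for the whole period since the last questionnaire, one interrupted session and daily interruption both give a yes.
- **The period is open.** One family may answer for yesterday and another for six weeks. At baseline there is no preceding study period, so a change from baseline may partly be a change in the period considered.
- **The event is undefined.** An interruption could be a break within a session or a missed session.

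A finding of no difference in interruptions would then be hard to interpret: it could reflect no effect, a coarse item, or families answering different questions.

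**Working it through.** The documents give no interruption rate, effect size or power for this item, so there is no figure of the plan's to reproduce. The check compares response formats under assumed rates.

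**Inputs from the documents**
- 13 children per group (Sample size; set for perceived duration of the routine, not for this item).
- Daily sessions (Background) and six weeks between questionnaires (Intervention): 6 × 7 = 42 prescribed sessions at one per day.
- Adherence below 50% (Hypothesis): at half, 42 × 0.5 = 21 sessions started, and 14 × 0.5 = 7 in two weeks.
- 5% significance (Statistical analysis), taken as two-sided.

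**Assumptions**
- Mean per-session interruption rates of 40% v 20%, 20% v 10% and 10% v 5%.
- Each child's own rate follows a beta distribution with a + b = 5.
- One pair of arms is compared. With two groups, Kruskal-Wallis is equivalent to Mann-Whitney.

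**Step 1: chance of a yes.** For any interruption in k sessions, P(yes) = 1 − B(a, b + k)/B(a, b), where B is the beta function.
- Mean 40% (a = 2, b = 3): 1 − 12/[(3 + k)(4 + k)]. At k = 42 this is 1 − 12/(45 × 46) = 0.994; at k = 21 it is 1 − 12/(24 × 25) = 0.980.
- Mean 20% (a = 1, b = 4): 1 − 4/(4 + k). At k = 42 this is 1 − 4/46 = 0.913; at k = 21 it is 1 − 4/25 = 0.840.
- The same formula at k = 42 gives 0.697 for a mean of 10% and 0.446 for 5%.

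If the item is read as whether the routine is usually interrupted (own rate above one half), the chances at 40% v 20% are 0.3125 and 0.5⁴ = 0.0625.

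**Step 2: power.** For yes/no answers, each arm's count is binomial (13, P). Power is the total probability of the tables with Fisher p < 0.05. For counts, beta-binomial data were simulated and compared by Mann-Whitney; ranges show the spread between separate runs.

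| Assumed mean rates | Yes/no, any in 42 | Yes/no, any in 21 | Count over 14 sessions | Count over 7 sessions |
|---|---|---|---|---|
| 40% v 20% | 99% v 91%: under 1% | 98% v 84%: 3–4% | 61–62% | 52% |
| 20% v 10% | 91% v 70%: 14% | 84% v 59%: 18% | 33–35% | 26–27% |
| 10% v 5% | 70% v 45%: 18–19% | 59% v 36%: 16% | 19–20% | 14% |

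Read as usually interrupted, the yes/no has about 20% power at 40% v 20%.

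**Step 3: would a window alone be enough?** A yes/no limited to 14 sessions gives Fisher power of 9%, 19% and 14% in the three scenarios. In the first two, most of the gain comes from the count, not from the window.

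**The case against.** A reader might infer that nearly every family will answer yes, so that the item cannot separate the arms. The documents do not support this.

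- **No rate is given.** A ceiling needs both a long window and frequent interruptions. If every child had the same per-session rate of 5% or 10%, the chance of a yes over 42 sessions would be 1 − 0.95⁴² = 88% or 1 − 0.90⁴² = 99%. With the child-to-child variation used above it is 45% or 70%, which is no ceiling. At 20% v 10% the arms still differ by 91% v 70%.
- **The 42-session window is inferred.** The item sits among questions about the usual routine and may be read that way. The annex appears to list item labels, so the wording families see may say more. Adherence below 50% would also mean fewer sessions available to be interrupted.
- **Much of the low power comes from 13 per arm.** At 10% v 5%, with no ceiling, both formats are weak. If half the sessions are missed, the count is slightly worse there (14% v 16%).
- **The item is one of four.** The adherence objective does not rest on it, and it is not the sample-size variable.

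All of this stands, and it limits the point. It does not remove it: the plan supplies neither a definition nor a window, although it sets a window for symptoms, and no other item records broken-off sessions.

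**Conclusion.** The point holds as an inexpensive improvement to one secondary adherence item. As written, the item discards the frequency of interruptions and leaves both the event and the period to each family.

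The loss depends on how common interruptions are. It is large at assumed rates of 40% v 20% (under 1% to about 20% power for the yes/no, depending on how it is read, against about 61% for a 14-session count). It is moderate at 20% v 10% (about 14% against 33%) and absent at 10% v 5% (about 19% each). These figures rest on assumed rates, an assumed spread between children, one pairwise comparison without adjustment for three arms and, for the 14-session count, every daily session being started. Saturation of the item is possible but not shown. The missing definition and window can be read directly from the documents and need no assumption.

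**What to change.** At all three questionnaires, define an interruption as a started session that was stopped or broken off before its end, distinct from a session not done. Then ask for two numbers covering the previous two weeks: sessions started and sessions interrupted. This matches the window of the symptom items and gives baseline and follow-up the same reference period.

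Analyse the per-child count or proportion as a quantitative variable with methods already in the plan: Kruskal-Wallis between groups and Wilcoxon within group. Because music may also change how many sessions are started, report that number alongside.

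Two weeks is preferable to one: halving the sessions counted from 14 to 7 lowers power from about 61% to 52% at 40% v 20%. The cost is one changed questionnaire line, slightly more recall effort, and no information on the earlier weeks of each six-week period. No extra visit is needed.

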**- Development of the instrumental therapeutic music:**

An instrumental therapeutic music will be developed specifically to the CF children from the Pediatric Pulmonology Unit at Malaga Regional Hospital to use as an adjunct to each part of the CPT routine according to the CPT strategy of this Unit.

The CPT treatment in this Unit is divided into 3 sections with a total length of about 40 minutes: During the first part, children should be relaxed while the nebulizer inhalation treatment is applied around 10-15 minutes. Next, airway clearance techniques are administered during 20-30 minutes to promote mucus expulsion. Finally, a new relaxation phase of about 5 minutes is proposed, where antibiotic nebulizer treatment is administered if necessary.

The music will be divided into 3 sections related to the 3 parts of the CPT routine:

- Section A: nebulizer treatment
- Section B: CPT work-bronchial clearance
- Section C: relaxation-nebulization

The professional musician will compose, and score-write the different music pieces according to the clinical recommendations from the research group. The composition of about 10 pieces is estimated.

After that, the musician with higher percussion studies will perform the songs with pitched percussion instruments (marimba, vibes, glockenspiel and xylophone) and unpitched percussion instruments (drums, congas, bongos, multi-percussion set and small-percussion instruments).

To record the audio, a portable studio (Tascam) and specific microphones will be used. Subsequently, the audio will be edited with the Cakewalk Sonar Platinum edition software and compiled in an audio-CD that will be use by participants in the intervention group.

#### **- Intervention:**

After participant recruitment they will complete the baseline questionnaire and be asked to carry out the CPT routine during 6 weeks (Grasso et al, 2000; Canga et al, 2015) as follow:

- Intervention group or TG: Using the Music-CD as an adjunct to each part of the CPT routine. The Music-CD will be provided after baseline questionnaire.
- Control group without music or CG: Continuing with the usual CPT without modifications.
- Control group with music or PG: Using commercial music as an adjunct to each part of the CPT routine.

As has been comment, the CPT treatment in this Unit is divided into 3 sections with a total length of about 40 minutes: During the first part, children should be relaxed while the nebulizer inhalation treatment is applied around 10-15 minutes. Next, airway clearance techniques are administered during 20-30 minutes to promote mucus expulsion. Finally, a new relaxation phase of about 5 minutes is proposed, where antibiotic nebulizer treatment is administered if necessary.

Participants in every group will continue with their usual treatment regimen without modifications. Follow-up changes or treatments modifications are not planned in any case.

A second questionnaire will be completed after 6 weeks and participants will continue managing the CPT routine in the same way during a new 6-week period. After that, the final questionnaire will be completed (Grasso et al, 2000) and the music-CD will be offered to CG and PG participants.

#### **- Statistical analysis:**

Statistical analysis will be performed using SPSS Software.

Initially a descriptive analysis of the study variables will be carried out, the values of the continuous variables will be summarized in a table where their corresponding means and standard deviation will be shown. The categorical variables will be presented in absolute and relative frequencies.

To compare qualitative measures Chi-square or Fisher tests will be used, and ANOVA or Kruskal-Wallis tests to quantitative.

To contrast the differences in the evolution of the variables between the different groups the multivariate analysis of variance test of repeated measures (MANOVA) will be applied with a factor between subjects (group) and a factor intra subjects (different moments of the intervention). Depending on the compliance of the sphericity condition, the Greenhouse-Geisser correction will be used. To contrast the differences between baseline and final measures in each group Wilcoxon test will be applied. To compare response to using music after the intervention into TG and PG, Mann–Whitney U test was used.

To compare response to using music after the intervention into TG and PG, Mann–Whitney U test will be used.

A significance of 5% ( $p < 0.05$ ) will be required to consider a difference as statistically significant.

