**- Sample size:**

To calculate the sample size, the perception of time taken to complete the routine has been assumed as main variable. According to Grasso et al, (2000) where the control group values in this variable were  $0.2 \pm 10.2$  (mean  $\pm$  SD), considering these values as baseline, a power of 80 %, a confidence level of 95 %, and a similar variability at the end of the study, a difference of 8 minutes would be considered as statistically significant with a sample size of 13 subjects. A total of 39 participants are necessary.

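### The repeated-measures MANOVA uses baseline as an outcome level in a 4-df group-by-time test; a baseline-adjusted model with one pre-set target would usually be more efficient, by an amount that depends on effect timing

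*Combined protocol and SAP*

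**What the plan says.** The Sample size section states that "the perception of time taken to complete the routine has been assumed as main variable". It assumes an SD of 10.2 with "a similar variability at the end of the study", "a power of 80 %, a confidence level of 95" %, and concludes that "a difference of 8 minutes would be considered as statistically significant with a sample size of 13 subjects".

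The Randomization section sets three groups: composed music (TG), no music (CG) and commercial music (PG). The Data collection and Intervention sections set three questionnaires, at baseline, 6 weeks and 12 weeks. On the middle one: "A second questionnaire will be completed after 6 weeks and participants will continue managing the CPT routine in the same way" for a further six weeks.

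To compare how the variables evolve between groups, the Statistical analysis section says "the multivariate analysis of variance test of repeated measures (MANOVA) will be applied with a factor between subjects (group", with the time points of the intervention as the within-subject factor. It adds: "Depending on the compliance of the sphericity condition, the Greenhouse-Geisser correction will be used". The section also lists ANOVA or Kruskal-Wallis for quantitative comparisons, Wilcoxon tests of baseline against final values within each group, and a Mann-Whitney test of TG against PG on the response to music.

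It names no baseline-adjusted model, no primary time point, no pairwise contrast for perceived time and no rule for missing questionnaires.

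**The concern.** In a randomised trial the groups have the same expected baseline. Used as a covariate, baseline removes noise from the follow-up comparison. Used as one level of the outcome, it adds its own noise to every change. The interaction also spreads the test over (3−1)(3−1) = 4 df and yields no single estimate, such as the TG–CG difference in minutes at 12 weeks. With 13 children per arm there is little information to spare.

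Two gaps in the text add to this. The multivariate test does not assume sphericity and Greenhouse-Geisser corrects the univariate F test, so the plan does not say which of the two will be reported. And a classical repeated-measures ANOVA or MANOVA normally uses only children with all three forms, while the plan is silent on what happens to the others.

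**Working it through.** **The plan's own figure.** The one-sample (paired) formula gives n = (10.2 × 2.8016 / 8)² = 12.76, rounded up to 13, which reproduces the stated size. Comparing two groups needs 2 × 12.76 = 25.52, so 26 per group.

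**Inputs.** From the documents: n = 13 per arm, 8 minutes, SD 10.2 (σ² = 104.04), three groups, three visits, two-sided 5% (sidedness assumed). Not in the documents and therefore assumed: correlation ρ between visits of 0.3, 0.5 or 0.7, equal for all pairs; 10.2 read as the SD of a raw value; an effect in TG only; and the timing of the effect.

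**Planned test.** F on 4 and (39−3)×2 = 72 df, with noncentrality λ = 13 × (2/3) × SS / [σ²(1−ρ)]. SS is the sum of squared deviations of the TG effect profile from its own mean: 42.67 for (0, 8, 8) and for (0, 0, 8), and 32 for (0, 4, 8). At ρ = 0.5 with a sustained effect, λ = 369.8 / 52.02 = 7.11, power 52%.

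**Baseline-adjusted TG–CG contrast.** The residual variance is σ²(1−ρ²) at week 12 and σ²[(1+ρ)/2 − ρ²] for the mean of both follow-ups. SE² = residual variance × (2/13) × (1 + 1/34), with 35 df. At ρ = 0.5:
- Week 12: SE = √(78.03 × 0.1538 × 1.0294) = 3.52; 8/3.52 = 2.28; power 60%.
- Follow-up mean: SE = √(52.02 × 0.1538 × 1.0294) = 2.87; 8/2.87 = 2.79; power 77%. If the effect appears only at week 12, the mean difference is 4 minutes: 4/2.87 = 1.39; power 27%.

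| TG effect at weeks 0, 6, 12 | Planned test | Week 12, adjusted | Follow-up mean, adjusted |
|---|---|---|---|
| 0, 8, 8 | 38 / 52 / 77% | 52 / 60 / 76% | 73 / 77 / 89% |
| 0, 4, 8 | 29 / 40 / 62% | 52 / 60 / 76% | 48 / 53 / 67% |
| 0, 0, 8 | 38 / 52 / 77% | 52 / 60 / 76% | 25 / 27 / 36% |
| 0, 8, 0 | 38 / 52 / 77% | 5 / 5 / 5% | 25 / 27 / 36% |

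(Entries are for ρ = 0.3 / 0.5 / 0.7.) Simulation with the Greenhouse-Geisser correction agrees to within a few points. Under no effect, the simulated type I error of all the tests was 4.4% to 5.1%.

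**Is the gain only a matter of testing one contrast?** No. A three-group 2-df test on the baseline-adjusted follow-up mean, with a sustained effect, gives 76 / 81 / 92% in simulation against 37 / 52 / 76% for the planned test, a gain of 39, 29 and 16 points. The single contrast in the table gains about 35, 25 and 12.

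**Other correlation pattern.** With correlation that decays over time (AR(1)) at 0.7 and a sustained effect, the week-12 adjusted test and the planned test both have 61%, so there is no gain.

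**Other reading of the SD.** If 10.2 is the SD of a change, then at ρ = 0.7 (equal correlation, sustained effect) the planned test has about 50%, the week-12 contrast 55% and the follow-up mean 70%.

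**Missing forms.** If 10% of children miss each follow-up form independently (assumed), 0.9 × 0.9 = 81% have all three: 39 × 0.81 = 31.6 children, or 10.5 per arm. With 10 or 11 per arm and ρ = 0.5, the planned test falls from 52% to about 39–41%.

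**The case against.** The best defence is that the planned test holds its error rate and matches the stated hypothesis, which expects differences among three groups. It also detects effects that change over time, which averaging dilutes. All of this stands. The table shows the averaged contrast doing clearly worse than the planned test when the effect is present at only one follow-up, and the documents do not say when the effect should appear.

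A reader might infer that baseline adjustment by itself recovers most of the missing power. The figures do not support that. At week 12 the gain shrinks to nil at ρ = 0.7. The large gains come from averaging two visits on fewer df, and they need a sustained effect.

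A reader might also infer that the plan discards children with an incomplete set of forms. The text does not say so. It names SPSS but no procedure and no missing-data rule. Deletion is the usual behaviour of the named method, and attrition bias is possible but not shown. A single-visit ANCOVA would also lose children who miss that visit.

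That baseline is a level of the time factor is implied, not spelled out. The alternative is less plausible: with only weeks 6 and 12 as levels, the interaction would miss a sustained effect altogether.

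The Greenhouse-Geisser point is mainly one of wording. In simulation the corrected univariate test and Wilks' test differed by at most about 3 points of power.

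Finally, the power figures come from ANCOVA, not from the mixed model proposed below. With complete data the two should be close.

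**Conclusion.** The concern holds as one of efficiency and specification, not validity. The plan collects a baseline value and does not adjust for it, tests a 4-df interaction with no stated target, pairs a multivariate label with a univariate correction, and leaves missing forms unaddressed.

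With 10.2 read as a raw SD, 13 per arm and correlations of 0.3 to 0.7, the change in power against the planned test is:
- Week-12 baseline-adjusted difference: about 0 to +25 points when an effect is present at week 12.
- Follow-up average: about +15 to +40 points if the effect is sustained (nearer +12 at the low end for a single contrast), about +5 to +20 if week 6 shows half the effect, and a loss of about 10 to 40 if the effect appears only at week 12.

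These ranges rest on assumed correlation and timing and should be reported as such.

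The change should not be read as curing the sample size. For 80% power at week 12, TG against CG, the baseline-adjusted size is 25.52 × (1−ρ²), or 24 / 20 / 14 per arm. If 10.2 is a change SD it is 25.52 × (1+ρ)/2, or 17 / 20 / 22. The plan has 13.

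**What to change.** For quantitative outcomes, replace the MANOVA as the main between-group analysis with a linear mixed model on the 6- and 12-week values:
- Fixed effects for baseline value, group, time and group-by-time, with unstructured covariance.
- Every randomised child with a baseline and at least one follow-up form included, and this stated as the missing-data rule.
- One target fixed before the data are seen. The week-12 group difference is the safer choice because it is robust to a delayed effect. The follow-up average should be chosen only if a sustained effect is expected, with the reason given.
- TG–CG and TG–PG differences reported with 95% confidence intervals under a stated testing order.
- The sphericity sentence deleted.
- Any power statement given as a range over correlation and timing.

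The cost is analysis wording and modest SPSS syntax, with no new visits, data or children. There are two downsides. The model assumes that forms are missing at random. And a week-12 target would miss an effect that is present at week 6 and gone by week 12, so the week-6 difference should be shown alongside as secondary. The sample-size calculation needs its own correction.
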